## Methods/Design

### Study design and setting

The proposed study relies on a participatory research approach which will combine quantitative and qualitative assessments. The impacts of the lifestyle program that will be developed will be assessed using a randomized controlled trial in one academic center. The study was registered to ClinicalTrials.gov (NCT01483612).

The RCT will be conducted at the CHUS fertility clinic, a fertility clinic with satellite access to IVF. The clinic offers care to patients with a range of reproductive problems including infertility, recurrent pregnancy loss, anovulation, PCOS, hyperprolactinemia, endometriosis, etc. The clinic has a successful ovulation induction and superovulation program including intrauterine insemination and access to donor sperm. Since 2011, it offers an IVF program in collaboration with Procrea Cliniques initially, and subsequently with the assisted reproduction center of the CHU Ste-Justine, where only the egg retrievals and embryo transfers are performed (evaluation of patients, protocol prescription, monitoring and decision making before and during cycles is done in Sherbrooke). Clinical outcomes and costs will be compared to a randomly assigned control group and to similar women seen in three fertility clinics across Canada not offering specific weight loss interdisciplinary lifestyle program: 1) an intra-provincial clinic (Procrea Cliniques, Montreal) with public coverage of fertility treatments; 2) 2 extra-provincial clinics (Centre for Fertility and Reproductive Health and IVF Unit at Mount Sinai Hospital, Toronto; and Fertility Clinic of Royal Alexandra Hospital, Edmonton) without public coverage of fertility treatments. These centers offer the full range of ART on site.

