### Evaluation of clinical outcomes of the lifestyle program for obese infertile women (Objective 2)

The **primary outcome** will be live-birth rates at 18 months. **Secondary outcomes** will be sub-divided into four categories of clinical outcomes:***Lifestyle and anthropometric outcomes***: evolution of anthropometric measures, changes in lifestyle habits (diet, exercise, sleep, alcohol, and tobacco), physical fitness level, daily energy expenditure from physical activities, time spent in various physical activity intensities, step count, evolution of readiness for change, quality of life.***Fertility outcomes***: pregnancy rate (biochemical pregnancy confirmed by a positive beta-human chorionic gonadotropin (β-hCG) level in the serum), spontaneous abortions, multiple pregnancies, spontaneous vs. ART-induced pregnancy, doses of fertility medications, number of treatment or IVF cycles.***Pregnancy adverse outcomes***: gestational diabetes, hypertension, pre-eclampsia, thromboembolism, caesarean section.***Neonatal outcomes***: birth weight, hypoglycemic episodes, Apgar score, jaundice, admission to neonatal intensive care, congenital defects, intrauterine death.

The results obtained at the CHUS will also be compared to those of women with the same criteria who will be seen in three fertility clinics across Canada. At the CHUS, primary and secondary outcomes will be determined using patients’ assessments, questionnaires and review of patients’ records. At the comparative clinics, charts of patients seen during the same time period will be retrospectively reviewed, and administrative data will be gathered.

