### Data analyses and interpretation

For objectives 1–2, all comparisons between randomized groups at the CHUS will follow both the intent-to-treat and/or per-protocol principles, and will consider results at the end of study. For repeated measures, the last-observation-carried-forward method will be used for women who drop out or become pregnant (depending on analyses). Time-to-event analyses will also be performed for fertility outcomes, with censoring for drop out alone, as well as for anthropometric outcomes, with censoring for both drop out and occurrence of pregnancy. Univariate analyses will compare the change in a variable in the intervention group with the change in this variable in the control group, using two-tailed unpaired *t* tests (for continuous variables) and chi-square or Fisher’s exact tests (for categorical variables). Changes in weight will also be compared for the same follow-up duration with changes for women seen at the other fertility clinics, using ANOVA tests. For the other variables, only end-of-study comparisons will be performed between the two groups in Sherbrooke and the three other fertility clinics, using ANOVA tests (for continuous variables) and logistic regressions (for categorical variables). Bonferroni-corrected p-values will be performed to adjust for the multiplicity of comparisons and an α level of 5 % will be considered significant for all analyses. Continuous variables that are not normally distributed will be log-transformed in order to ascertain normal distribution. Multivariate analyses will also be used in order to adjust for baseline differences and for potential confounders, and to determine independent predictors of outcomes. Triangulation will be performed between quantitative and qualitative data.

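### Clinic comparison: follow-up is matched for weight but not for live birth and the other outcomes, so unequal observation time could look like a clinic difference

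*Protocol article*

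**What the plan says.** The section Data analyses and interpretation of the protocol article treats the external comparison in two adjacent sentences. On weight: "Changes in weight will also be compared for the same follow-up duration with changes for women seen at the other fertility clinics". On the rest: "For the other variables, only end-of-study comparisons will be performed between the two groups in Sherbrooke and the three other fertility clinics", using ANOVA for continuous and logistic regression for categorical variables. Earlier in the same section, time-to-event analysis with censoring for dropout is planned for fertility outcomes. The section also states: "Multivariate analyses will also be used in order to adjust for baseline differences and for potential confounders".

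The Objective 2 section on clinical outcomes says that the primary outcome "will be live-birth rates at 18 months", and that trial results will be "compared to those of women with the same criteria who will be seen in three fertility clinics across Canada". On the data source there it says: "charts of patients seen during the same time period will be retrospectively reviewed, and administrative data will be gathered". Table 2 lists live birth, fertility, pregnancy, neonatal and most cost variables at those clinics simply as retrospective.

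For trial women the clock is defined: the abstract limits follow-up to 18 months or the end of pregnancy. No such rule is given for chart women.

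**The concern.** Live birth, pregnancy and treatment cycles accumulate, so the proportion or count seen at any reading depends on how long a woman has been observed. Being seen in the same calendar period does not equalise this: a woman first seen late in the period contributes little time, and one first seen early contributes more. The authors saw the issue for weight and matched duration there. The next sentence confines the remaining variables to an end-of-study reading, and the word *only* appears to rule out the time-to-event approach for this contrast.

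The reading time matters all the more because women in the programme arm defer other fertility treatment for six months, so their outcomes are shifted later than under usual care.

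At stake are the external parts of Objectives 2 and 3 and the generalisability argument in the Discussion. Cost per live birth depends on observation time twice, through costs accrued and through births counted. The analysis section does not say outright whether cost belongs among the other variables, but the cost comparison uses the same charts and no separate horizon is stated for it. The limitations paragraph names evaluation bias, recall bias and coverage differences, but not unequal follow-up.

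**Working it through.** **1. The plan's own figure.** The Sample size section gives 25 % against 50 %, α = 5 %, power 80 %, 58 per group. Two-sided, pooled variance, no continuity correction:

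n = [1.960·√(2·0.375·0.625) + 0.842·√(0.25·0.75 + 0.50·0.50)]² / 0.25² = (1.342 + 0.557)² / 0.0625 ≈ 57.7, so 58.

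Power at 58 per group is 80.2 %, and 116 × 1.10 = 127.6 gives the stated 128. The figure reproduces, but it concerns the randomised contrast only. No sample size or follow-up figure is given for the clinic comparison.

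**2. What each group's clock is.**

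| | Start | Horizon | Pregnancy in progress |
|---|---|---|---|
| Trial groups | randomisation, after baseline assessment | 18 months | followed to its end |
| Chart women, weight change | not given | same duration as the trial | not given |
| Chart women, all other outcomes | not given | end of study | not given |

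**3. Illustration with no true difference.** Inputs: 25 % live birth at 18 months (from the sample-size section). Assumed, because the article is silent: a constant rate, clinic follow-up of 12 or 24 months, and clinic samples of 64 to 200 women. The trial group is taken as 64 (128 / 2).

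h = −ln(0.75) / 18 = 0.01598 per month; P(t) = 1 − exp(−h·t)

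- P(12) = 1 − exp(−0.1918) = 17.5 %
- P(18) = 25.0 %
- P(24) = 1 − exp(−0.3836) = 31.9 %

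The gaps from the trial's 25 % are 25.0 − 17.5 = 7.5 and 31.9 − 25.0 = 6.9 points. The odds ratios are (0.175/0.825)/(0.25/0.75) = 0.63 and (0.319/0.681)/(0.25/0.75) = 1.40.

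**4. Effect on the test.** With d the difference, se₀ the pooled and se₁ the unpooled standard error, the two-sided rejection rate is Φ((d − 1.96·se₀)/se₁) + Φ((−d − 1.96·se₀)/se₁). For 12 months and 64 per group: d = 0.0755, se₀ = 0.0723, se₁ = 0.0720, giving 18 %. The ranges below run from 64 to 200 clinic women, before any Bonferroni correction:

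| Clinic follow-up | Live birth | Odds ratio | Rejection with no true difference |
|---|---|---|---|
| 12 months | 17.5 % | 0.63 | 18–28 % |
| 18 months | 25.0 % | 1.00 | 5 % |
| 24 months | 31.9 % | 1.40 | 14–17 % |

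**5. Sensitivity.** If no live birth can occur before month 9 and the 18-month figure stays at 25 %, h = −ln(0.75)/9 = 0.03196. Twelve months then gives 1 − exp(−3h) = 9.1 % and 24 months 1 − exp(−15h) = 38.1 %. The direction is the same and the gaps are larger. When both groups are read at 18 months the rejection rate returns to 5 % in every scenario.

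**The case against.** The best counter-reading is that *end of study* is set against *change*. The preceding sentences compare changes, charts may lack baseline values for most variables, and so only end values are compared. With the primary outcome defined at 18 months, that horizon may be meant for chart women too. An article may also leave index dates and abstraction windows to the full protocol. This reading is possible, and it is why unequal follow-up cannot be called a fact: nothing in the article says that chart women are observed for different lengths of time. But nothing extends the 18 months to them either. The article also does more than stay silent, since it prescribes equal duration for one variable and an end-of-study reading for the rest.

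Several stronger readings are tempting and are not supported:

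- *Case mix is left uncontrolled.* Chart women must meet the same criteria in the same period, and multivariate adjustment for confounders is planned. It is stated in general terms and not tied to this contrast. It would not in any case correct for time observed, but it is not absent.
- *A five-group ANOVA blends the randomised test with the clinic contrast.* The randomised groups are tested separately by t, chi-square or Fisher tests, and the Bonferroni correction suggests several contrasts.
- *Table 2 rules out the weight test.* Its N/A entry covers the study-visit measurements. The Medical records section, headed as applying to all sites, abstracts weight from charts at each visit.
- *Trial patients are in the comparator's charts.* The section Study design and setting says of the IVF arrangement: "it offers an IVF program in collaboration with Procrea Cliniques initially". It also says that only retrievals and transfers take place at the partner, with evaluation and monitoring in Sherbrooke. Overlap is possible, not shown.

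**Conclusion.** The concern holds for the secondary, non-randomised comparison. Followed as written, differences in live birth, fertility, pregnancy and cost outcomes between the trial groups and the clinics could reflect time observed alone. The illustrated size is about 7 percentage points either side of 25 %, with rejection rates of 14–28 % instead of 5 %. This rests on a constant rate, on clinic follow-up of 12 or 24 months, on 64 to 200 clinic women and on an uncorrected test, none of which the article fixes. Bonferroni correction would lower the rejection rates but leave the bias.

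A reader might set the 14.4-point spread between 12 and 24 months (31.9 − 17.5) against the planned 25-point effect. That spread lies between two hypothetical clinics, and the 25 points belong to the randomised test. A reader might also infer that the trial's main result is in doubt. It is not: both randomised groups share one clock and one horizon. Nor do Objectives 2 and 3 depend solely on the clinics, since each also names the randomised control group. The point deserves correction, but it does not threaten the primary analysis.

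**What to change.** Replace the end-of-study sentence with a rule that gives all five groups one clock:

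- **Start:** randomisation at the trial site; elsewhere, the first visit in the period at which the woman meets the eligibility criteria.
- **Horizon:** 18 months from that date, with the trial's rule for pregnancies still in progress applied to everyone. Alternatively, extend the time-to-event analysis already planned for fertility outcomes to this contrast, censoring at the last chart entry. State that costs are accrued over the same window.
- **Adjustment:** say that the planned multivariate adjustment applies here, for example for age, BMI, PCOS and infertility cause.
- **Label:** report the result as non-randomised.

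Two minor items can be settled at the same time. Add a footnote to Table 2 so that its N/A entry agrees with the chart weights collected at all sites. Check the intra-provincial clinic's charts for trial-site IVF patients, and leave out any that are found.

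The cost is an abstraction rule and some wording, with no new patients. The drawback is that charts with short follow-up are censored, which reduces the information from the clinics.

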### Sample size

Our sample size estimation is based upon our primary outcome (see Objective 2), which is live-birth rates between randomized groups at the CHUS. Based on the Fertility Fitness Program, the inclusion of 58 women per group will provide our study a power of 80 % to identify a doubling in live-birth rates with our program (25 to 50 %, α = 5 %). Assuming a dropout rate of 10 % (these women are usually highly motivated), our final estimated sample size will be 128 women. For other objectives and outcomes, it would be difficult to assess power because similar evaluations have not been previously reported.

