Although this research protocol is innovative and uses a robust methodology, some limitations need to be acknowledged. First, implementation and outcome evaluation of the lifestyle program will take place in a single clinic. However, a RCT at the CHUS will be performed with sufficient power to assess the primary outcome. Results will also be compared to three other clinics, which is an ideal first step for the future development of a multicenter RCT. It is important to appropriately design and evaluate the program in one center before transferring it to other centers. Second, some of the outcome measures will be self-reported and might be biased. However, such bias should be similar in both randomized groups and the results will be triangulated with data from many different sources (administrative data, questionnaires, focus groups, etc.). Third, most of the outcomes will be assessed only retrospectively in the clinics of comparison. This might introduce an evaluation bias although multiple sources of information will be used and compared. A recall bias is also possible for the evaluation of costs for the patients’ viewpoint in these clinics, but the same estimations will be performed in Sherbrooke and compared with real costs, which will allow the determination of the degree of this bias for comparison clinics. Fourth, in Sherbrooke, fertility treatments, including IVF, will be covered by the public health care system. Therefore, some results may not reflect all North American fertility clinics, but the same results will be compared to clinics in other provinces where fertility treatments are not covered.

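### The Bonferroni rule has no defined family and does not exempt the primary test, so it is not reconciled with a sample size computed at an uncorrected 5 %

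*Protocol article*

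**What the plan says.** The protocol article names a single primary outcome under Objective 2: it "will be live-birth rates at 18 months". Four categories of secondary outcomes follow, and the same section plans comparisons with three external fertility clinics.

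Under Data analyses and interpretation, categorical variables are compared between the randomised groups by chi-square or Fisher's exact test. End-of-study comparisons across the two Sherbrooke groups and the three clinics use ANOVA or logistic regression. The next sentence reads: "Bonferroni-corrected p-values will be performed to adjust for the multiplicity of comparisons and an α level of 5 % will be considered significant", and it ends by extending that threshold to all analyses. It gives no family, no number of comparisons and no exemption.

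The Sample size section rests on live birth between the randomised groups. It takes 58 women per group to give "a power of 80 % to identify a doubling in live-birth rates with our program", from 25 to 50 % at α = 5 %, with no correction mentioned. A 10 % dropout allowance brings the total to 128. The Discussion then relies on this, stating that "a RCT at the CHUS will be performed with sufficient power to assess the primary outcome".

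**The concern.** A Bonferroni rule stated generally and a sample size computed at an uncorrected 5 % agree only if the primary test lies outside the rule. The article does not say that it does. If the test lies inside, the primary result is judged at a smaller α than the one it was sized for, and power is below the stated 80 %.

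The decision rule is also at stake. With the scope open, a primary p-value between 0.05/k and 0.05 could be called significant or not from the same sentence, after the data are known. For k = 10 that zone runs from 0.005 to 0.05. A single primary outcome, tested once between two arms, needs no correction for secondary outcomes, so including it would lose power without improving control of the primary error rate.

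**Working it through.** **Inputs from the article.** Live-birth rates 25 % and 50 %, α = 5 %, power 80 %, 58 per group, 10 % dropout, total 128 (Sample size). Sidedness is not given for the sample size. The analysis section is explicit only for t tests ("using two-tailed unpaired"), so two-sided is assumed.

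**Input assumed.** k, the number of comparisons in the Bonferroni family. The article gives none, so a range is shown.

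**Step 1: reproduce the stated size.** With pooled variance under the null and no continuity correction:

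n = [z(1−α/2)·√(2·p̄·(1−p̄)) + z(0.80)·√(p1(1−p1) + p2(1−p2))]² / (p2−p1)²

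p̄ = 0.375, so √(2 × 0.375 × 0.625) = 0.6847 and √(0.1875 + 0.25) = 0.6614.

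n = [1.96 × 0.6847 + 0.8416 × 0.6614]² / 0.25² = 57.7, that is 58 per group.

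The stated 58 therefore reproduces at an uncorrected two-sided 5 %. Other conventions do not give it: one-sided 46, unpooled variance 55, continuity-corrected 66. For dropout, 116 × 1.1 = 127.6, which gives the stated 128, or 64 per group. Division by 0.9 would give 129, an immaterial difference.

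**Step 2: power if the primary test is judged at 0.05/k.**

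Power = Φ{[0.25·√n − z(1−0.05/(2k))·0.6847] / 0.6614}

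For n = 58, 0.25·√58 = 1.9039. Two lines in full:
- k = 1: (1.9039 − 1.960 × 0.6847)/0.6614 = 0.850, power 80.2 %.
- k = 5: (1.9039 − 2.576 × 0.6847)/0.6614 = 0.212, power 58.4 %.

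| k (assumed) | α for the primary test | Power, 58 per group | Power, 64 per group | n per group for 80 % |
|---|---|---|---|---|
| 1 (exempt) | 0.05 | 80.2 % | 84.0 % | 58 |
| 2 | 0.025 | 71.2 % | 75.9 % | 70 |
| 5 | 0.01 | 58.4 % | 64.0 % | 87 |
| 10 | 0.005 | 48.9 % | 54.7 % | 99 |

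The k values are illustrations. Two could arise from counting an intention-to-treat and a per-protocol analysis of live birth. Ten is the number of pairs among the five groups (5 × 4/2), but the article does not say that all pairs will be tested.

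**Step 3: choice of test at an uncorrected 5 %.** Exact enumeration of the two binomials at 58 per group gives 79.9 % for chi-square and 74.3 % for Fisher's exact test. Only the former matches the stated power.

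**The case against.** The strongest reply is that the two sections already agree. There is one primary outcome, compared once between two arms, so that test has no multiplicity to correct. Grammatically, the phrase about all analyses attaches to the 5 % threshold and not to the Bonferroni clause. That clause directly follows the comparisons with the external clinics, where Bonferroni is an ordinary follow-up. Read this way, 58 per group is correct. The details of a multiplicity family are also commonly left to a full protocol or analysis plan, and neither is shown here.

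Much of this stands. A reader might infer that the 80 % power is simply not delivered. The article does not support that, because it never says that the correction applies to the primary test. A reader might also infer that a true doubling would more often than not be declared non-significant. At 58 per group that needs k of about 10 or more, and with all 64 per group power is still 54.7 % at k = 10. Nor does the article assign Fisher's exact test to live birth. Offering chi-square or Fisher's is customary wording, with Fisher's kept for sparse tables. Here the smallest expected count under the null is about 58 × 0.375 = 22, so chi-square is the natural choice.

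The reply does not remove the ambiguity. Live birth is also collected at the external clinics (Table 2), and intervention versus control is one pair within the five-group comparison. Even on the narrow reading, the primary contrast may therefore be corrected in one analysis and uncorrected in another, and nothing says which one decides. The point concerns a rule that the article does state, and its fit with a sample size that the article also states. It is not a complaint about detail left elsewhere.

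**Conclusion.** The point holds conditionally. The article states a general Bonferroni rule without a family or an exemption for the primary test, and does not reconcile it with a sample size computed at an uncorrected 5 %. The sample-size arithmetic itself is sound: with the primary test exempt and a chi-square-type test, 58 per group gives 80 %.

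If the correction reaches the primary test, any k of 2 or more takes power below 80 %, even if all 64 per group are analysed. The size of the loss cannot be fixed from the article because k is not given. All figures assume two-sided testing and true rates of 25 % and 50 %. The finding is an open confirmatory threshold, not a demonstrated loss of power.

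**What to change.** In Data analyses and interpretation, state that:

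- Live birth at 18 months is compared once between the randomised groups, at two-sided 5 %, without multiplicity correction. The test is of chi-square type and stratified by PCOS status, for example Cochran-Mantel-Haenszel, and not Fisher's exact test. PCOS is already the randomisation stratum. The article gives no stratum-specific rates, so the power of the stratified test is not computed here; the 80 % refers to the unstratified chi-square.
- Multiplicity control applies within defined families of secondary outcomes, for which the four named categories are the obvious choice. Holm replaces Bonferroni: it gives the same familywise error control and never has less power.
- Comparisons with the external clinics, including those on live birth, lie outside the confirmatory test.

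This takes a few sentences and needs no further patients or data. The Sample size section and the power statement in the Discussion can then stand.

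If the investigators do intend the correction to cover the primary test, they should state k and re-size at 0.05/k. With 10 % dropout (division by 0.9), the totals would be 156 for k = 2, 194 for k = 5 and 220 for k = 10.
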